**Methods:**

This is an assessor-blind, randomized control trial of 150 adolescent competitive female (9–19 years) soccer players. Each participant receives 3x/week neuromuscular preventive training and 1x/week biofeedback, the mode depending on their randomization to one of 3 biofeedback groups (hip-focused, knee-focused, sham). The primary aim is to assess the impact of biofeedback training on knee abduction moments (the primary biomechanical predictor of future ACL injury) during double-leg landings, single-leg landings, and unplanned cutting. Testing will occur immediately before the training intervention, immediately after the training intervention, and 6 months after the training intervention to assess the long-term retention of modified biomechanics. Secondary aims will assess performance changes, including hip and core strength, power, and agility, and the extent to which maturation effects biofeedback efficacy.

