### Hypotheses

Our central hypothesis is that biofeedback methodology will maximize the effectiveness of neuromuscular prophylactic interventions. More specifically, we hypothesize that ROBUST training (both knee- and hip-focused) will lead to significantly reduced knee abduction load during double-leg jump landings, but that hip-focused ROBUST training will significantly reduce knee abduction load during a high-risk unplanned cutting task compared to knee-focused training. Further, we hypothesize that participants that receive hip-focused ROBUST training will best retain improvements in knee abduction load six months following training.

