## Methods/design

### Study design

ROBUST is a prospective, randomized, active comparator, open blinded, end-point trial. Participants will be randomized into one of three study arms 1) hip-focused biofeedback, 2) knee-focused biofeedback, and 3) sham biofeedback. Each participant will provide written participant consent, and/or parental consent and participant assent as appropriate. All participants will be tested immediately before (pre-test), immediately after (post-test), and 6 months after (retention) a 6-week prophylactic neuromuscular training program. The training program will be performed 3 times a week, with augmented biofeedback (according to group designation) 1 time a week. All testing and training will occur at the High Point University Human Biomechanics and Physiology Laboratory. Figure 1 provides a flowchart of the design of ROBUST. Researchers responsible for collecting the primary outcome measures will be blinded to the participant’s group designation. While participants randomized to the study arms of the trial will not be blinded, we will also make every effort to maintain the blinding of the researchers responsible for delivering the interventions. In addition, the investigators and biostatistician will remain blinded to the group status during data management and analysis. In case a participant needs to be treated for an injury during the study period, the treating clinicians will not be aware of the group assignment. In addition, teams consisting of a trainer and blinded research assistants will be maintained as separate, functioning teams throughout the study to minimize the chances of unblinding. The study protocol was approved by the Institutional Review Board at High Point University. Additional information can be found at: Clinicaltrials.gov (Identifier: NCT02754700).

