### Data and statistical analysis

Intention-to-treat (ITT) analysis will be performed according to CONSORT statement guidelines [44]. Baseline differences between groups will be analyzed using an analysis of variance (ANOVA). Improvement in the biomechanical outcomes of knee load and hip-strategy will be assessed using Paired-*T* test (when normal) or Signed Wilcoxon rank-sum test (when non-normal) for each study arm. An ANOVA will be used to compare the improvement in post- vs. pre-training in knee load and the hip-strategies across the three study arms. Tukey’s multiple comparison procedures will be used to adjust for multiple comparisons. ANOVA analyses will consider adjusting for age and other baseline covariates as determined earlier. All ITT participants will be analyzed. Further, we will adopt multivariate ANOVA techniques, which will be modeling the study outcome measures as a whole in testing study hypotheses.

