### Timeline

Human subjects review board approval was obtained in November, 2015 from the High Point University Institutional Review Board. Recruitment and training began in June 2016. A projected 75 subjects will be enrolled in the study within the first year, followed by 75 participants in the 2^nd^ year. Final data collection is planned to be completed by June, 2018 and final analyses to be completed by April, 2019.

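### The six-month retention hypothesis has no matching between-arm comparison: the only one with stated occasions is post versus pre

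*Protocol article*

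**What the plan says.** The Hypotheses section of the protocol article ends with a comparison between arms at six months: "participants that receive hip-focused ROBUST training will best retain improvements in knee abduction load six months following training". The abstract gives the purpose of the last visit in the same terms, with testing "6 months after the training intervention to assess the long-term retention of modified biomechanics". Study design sets three separate occasions: "immediately before (pre-test), immediately after (post-test), and 6 months after (retention) a 6-week prophylactic neuromuscular training program".

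Data and statistical analysis lists three kinds of test of the biomechanical outcomes:

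- Within arm: "Improvement in the biomechanical outcomes of knee load and hip-strategy will be assessed using" a paired t-test or a Wilcoxon test for each arm. No occasions are named.
- Between arms: an ANOVA will "compare the improvement in post- vs. pre-training in knee load" and in hip strategy across the arms, with Tukey's procedure for multiple comparisons and possible adjustment for age and other baseline covariates.
- Multivariate: "we will adopt multivariate ANOVA techniques, which will be modeling the study outcome measures as a whole in testing study hypotheses". No occasion, outcome set or contrast is named.

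The section mentions neither the retention visit nor six months. On the calendar, Timeline gives a June 2016 start, 75 participants in each of two years, and this end date: "Final data collection is planned to be completed by June, 2018".

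**The concern.** The article fixes the occasions of its between-arm ANOVA, and those occasions do not match one of its own hypotheses. If the section is followed as written, no defined comparison between arms uses the six-month data. An analysis plan that copied the section faithfully would carry the mismatch forward.

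At stake is the claim about lasting effect, which is one of the three specific hypotheses and the reason for bringing participants back. Without a named contrast, two weak routes stay open. Retention could be judged by setting three within-arm p-values beside each other, which does not test a difference between arms. Or the contrast could be chosen after the data are seen. The phrase about retaining best can mean the smallest loss since post-test or the largest remaining benefit over pre-test, and the two can rank the arms differently. An arm that gained little has little to lose.

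**Working it through.** **1. Does any stated analysis compare arms at six months?**

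| Analysis | Between arms? | Occasion stated? | Answers which arm retains best? |
|---|---|---|---|
| Paired t or Wilcoxon | No, one arm at a time | No | No, even if run on six-month data |
| ANOVA with Tukey | Yes | Post versus pre | No; post-test is directly after training |
| Multivariate ANOVA | Presumably | No | Not as written; a joint test over several outcomes does not isolate knee abduction load at six months |

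Post cannot be read to include retention. Study design defines the two separately, and the Landing biomechanics text and the Fig. 4 caption also list them as separate sessions.

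**2. The plan's own power figure.** Inputs from Participants: 3 arms, 40 evaluable per arm, alpha 0.05, variance of means 0.082 in units of the common variance.

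- Cohen f = √0.082 = 0.286
- Noncentrality λ = 120 × 0.082 = 9.84
- Degrees of freedom: 2 and 120 − 3 = 117
- Power = P[F′(2, 117; λ = 9.84) > F(0.95; 2, 117)] = 79.8%

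This agrees with the stated 80% (41 per arm is the smallest number that reaches it). Other readings of 0.082 do not reproduce it: a variance with divisor k − 1 gives 61.3%, and 0.082 taken as f itself gives 11.4%. The dropout step also agrees: 40 / (1 − 0.20) = 50 per arm.

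**3. Could the six-month visit support a test?** The 40 per arm are those expected at the end of the study, so they already allow for loss up to the retention visit. The same ANOVA on retention minus pre, assuming the same standardized effect at six months, gives:

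| Alpha for six months | 40 per arm | 50 per arm |
|---|---|---|
| 0.05 | 79.8% | 88.5% |
| 0.025 (equal split with post, assumed) | 70.8% | 81.9% |

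These are powers of the overall three-arm F test, not of single Tukey-adjusted pairs.

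**4. Calendar check (conditional).** Training of 6 weeks plus 6 months is 42 + 183 = 225 days. Counting back from 1 June and 30 June 2018 gives 19 October and 17 November 2017. A participant pre-tested later than that cannot have a retention visit by June 2018. If second-year intake were even from June 2017 to May 2018 (assumption), 195/365 × 75 ≈ 40 to 224/365 × 75 ≈ 46 participants would fall after the cut-off. That is 27% to 31% of 150, against the 20% loss allowed. If intake is confined to summer 2017, the number is zero.

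**The case against.** The strongest reply is that this is a condensed article. Its full analysis plan is not shown, and naming a contrast for a second time point is often left to that plan. Data and statistical analysis never says that the post-versus-pre ANOVA is the only between-arm analysis, and its last sentence promises multivariate methods for the study hypotheses, of which retention is one. The paired tests are not limited to post versus pre either.

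Part of this stands. A reader might infer that the retention hypothesis has no analysis at all, or that the retention visit cannot answer its question. The documents support neither. The multivariate sentence does claim to address the hypotheses, all arms are measured at six months with the baseline methods, and the sample size covers loss to that visit.

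The reply does not remove the point. The article is not merely silent: it does fix an occasion for its between-arm test, and that occasion is the wrong one for a stated hypothesis. The multivariate sentence supplies no occasion or contrast that would repair this.

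Two further inferences should be resisted. One is that the plan commits the regression-to-the-mean error of comparing change from post-test to retention. It proposes no such analysis, and in randomized arms only the chance part of a post-test difference would fall back. The other is that 40 to 46 retention visits will be lost. That rests wholly on an assumed even intake. The Discussion calls the training an off-season program, which makes even intake doubtful, and Timeline states no enrolment pattern that contradicts its end date.

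**Conclusion.** The point holds as a mismatch between a stated hypothesis and the stated analysis. One of three specific hypotheses, the one on lasting effect, has no defined between-arm contrast, occasion or multiplicity rule. The post-test hypotheses are not affected, because a comparison across arms is given for them.

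The visit and the sample are adequate. About 79.8% power is available at six months with 40 per arm at 0.05, on the assumption that the standardized effect used for sizing persists and that loss stays within 20%.

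The calendar is something to verify, not an error shown: the end date is met or missed according to when second-year participants are pre-tested.

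**What to change.** Before the group codes are broken, replace the single post-versus-pre comparison by one repeated-measures mixed model of knee abduction moment at post-test and six months. Its terms are arm, visit, arm by visit, pre-test value (with its own effect at each visit) and age. Then:

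- Read the post-training hypotheses from the arm contrasts at post-test.
- Read the retention hypothesis from hip versus knee and hip versus sham at six months, both adjusted for pre-test. Sham belongs here because the hypothesis ranks the hip arm best of all.
- Apply Tukey's adjustment within each visit.
- State whether six months is a secondary test or shares alpha with post-test.
- Say what the multivariate ANOVA is for, or label it supportive.

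The model also keeps participants who attend only one of the two follow-up visits. An ANOVA of retention minus pre across arms would be a simpler way to close the gap, but it would not use the two visits together.

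Separately, check the second-year enrolment window against the cut-off of about mid-October to mid-November 2017. If intake ran later, restate the date for final data collection.

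Cost: a few sentences and slightly more analysis work, with no new measurements. If alpha is split equally, power at six months falls from 79.8% to about 71% with 40 per arm under the same effect. Naming six months as secondary avoids that loss but gives the retention claim lower standing.

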### Participants

One hundred fifty female soccer players between the ages of 9 and 19 will be recruited from local soccer clubs and high schools for this study. Recruitment will be performed primarily through discussions with club presidents, athletic directors, directors of coaching, coaches, and parents. The study sample will consist solely of female youth soccer players that participate on a competitive team at the time of enrollment. Participants will be excluded if they are not currently able to participate in sport due to an injury or cannot commit to participating in the 6-week intervention.

An equal sample size of *N* = 50 will be randomized to each of the three study arms. Assuming 20% of loss to follow up, a sample size of 40 is expected in each group at the conclusion of the study. Under this assumption, it was estimated that one-way analyses of variance will have 80% of power to detect at the 0.05 level a difference in means characterized by a variance of means of 0.082 (i.e. the averaged group mean deviations from the grand mean being 0.082 or higher of the common standard deviation). Previous results suggest an improvement in knee abduction load between two forms of biofeedback training with estimated mean+/-SD of 11+/-6 Nm vs. 2+/-10 Nm, indicating sufficient statistical power in this study [35].

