### Randomization

Enrolled subjects will be randomized to a biofeedback group using computer-generated blocks after completing pre-test screening. A clinical coordinator, independent of the study statistician and research assistants conducting the analyses, trainer, and evaluator, will generate a random sequence of numbers which will be stored in a spreadsheet accessible to only non-blinded study staff. Participants will be assigned to the study arms in the randomization scheme according to the order that their baseline visit was completed. The clinical coordinator will generically label the treatment assignments to group A, B, and C to ensure blinding is maintained for researchers responsible for pre- and post- testing, and for researchers responsible for providing the prophylactic intervention. Only the clinical coordinator and researchers responsible for providing ROBUST training will be privy to the participants’ group designation.

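### The plan promises to analyse all ITT participants, but the between-arm test it describes is a change-score ANOVA that uses only players with a follow-up test and is powered on the 40 per arm expected to remain

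*Protocol article*

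**What the plan says.** All statements are in the protocol article.

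- **Data and statistical analysis.** The analysis is declared to be ITT under CONSORT, with the sentence "All ITT participants will be analyzed". The set of ITT participants is not defined further. For the comparison of arms, "An ANOVA will be used to compare the improvement in post- vs. pre-training in knee load" and in the hip strategies, with Tukey adjustment and possible covariate adjustment. A multivariate ANOVA of the outcomes taken together is added.
- **Participants.** "One hundred fifty female soccer players between the ages of 9 and 19 will be recruited", and 50 of them "will be randomized to each of the three study arms". Then: "Assuming 20% of loss to follow up, a sample size of 40 is expected in each group at the conclusion of the study". On that assumption, "one-way analyses of variance will have 80% of power to detect at the 0.05 level"; the effect that this power refers to is given as "a difference in means characterized by a variance of means of 0.082" (in units of the common variance).
- **Randomization.** Players "will be randomized to a biofeedback group using computer-generated blocks after completing pre-test screening", so a pre-test is planned for every player before allocation.
- **Study design and Retention testing.** There are three test occasions: pre-test, post-test directly after the 6-week programme, and a retention test 6 months after training. The hypotheses include an arm difference in retention.

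**The concern.** A change score exists only for a player tested both before and after training. An ANOVA of change scores, taken as described, therefore leaves out any randomised player who missed the later test. A multivariate ANOVA in its standard form also leaves out a player who lacks any one of the outcomes. That is an analysis of players with available data, whereas the text promises an analysis of all ITT participants.

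Two things are at stake. The first is labelling: readers will take the result as covering all 150 randomised players. The second is possible bias. Participants are not blinded, and the study design foresees that some will need treatment for injury. The outcome tasks are landings and unplanned cuts, which an injured player may be unable to perform. The background section presents knee abduction moment (KAM) as the leading predictor of ACL injury. Loss related to the outcome is therefore conceivable. If it differs by arm, a contrast among those who remain can be shifted. The retention comparison is the most exposed, because loss has had the longest time to accumulate.

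**Working it through.** **1. Planned loss.** Inputs from Participants: 150 randomised, 50 per arm, 20% lost.

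- 50 × (1 − 0.20) = 40 per arm, or 120 in total.
- 150 × 0.20 = 30 lost.

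The article ties this loss to study end, which is the 6-month retention visit. It gives no separate figure for the post-test. If loss accumulates over time, 30 is the most that the plan foresees missing at the post-test.

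**2. Which sample the stated power belongs to.** For a one-way ANOVA with k = 3 arms of n players, at level 0.05, power is P(F′ > F crit). F′ is noncentral F with 2 and 3n − 3 degrees of freedom and noncentrality λ = 3n × 0.082. Here the variance of means is the sum of squared deviations divided by k, in units of the common variance.

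| n per arm | λ | Power |
|---|---|---|
| 40 | 120 × 0.082 = 9.84 | 79.8% |
| 50 | 150 × 0.082 = 12.30 | 88.5% |

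The plan's 80% is reproduced at 40 per arm and not at 50. Two other readings of 0.082 do not give 80% at 40 per arm: a variance with divisor k − 1 gives 61.3%, and 0.082 taken as the effect size f itself gives 11.4%. The power figure therefore treats the ANOVA as an analysis of 120 retained players.

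**3. When bias would arise.** Let d be the proportion lost in an arm, and g the mean improvement of those who stay minus that of those lost, in SD. The arm mean is (1 − d) × (mean of stayers) + d × (mean of lost), so the stayers' mean exceeds the arm mean by d × g. The bias in a contrast of two arms is d₁g₁ − d₂g₂. The documents give neither loss by arm nor g, so the following are assumptions:

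| Loss in the two arms | g | Size of bias (SD) |
|---|---|---|
| 20% and 20% | the same in both | 0 |
| 15% and 25% | 0.5 in both | 0.25 × 0.5 − 0.15 × 0.5 = 0.05 |
| 10% and 30% | 0.5 in both | 0.30 × 0.5 − 0.10 × 0.5 = 0.10 |
| 10% and 30% | 1.0 in both | 0.30 × 1.0 − 0.10 × 1.0 = 0.20 |
| 20% and 20% | 0.5 to 1.0 in one arm, 0 in the other | 0.20 × 0.5 to 0.20 × 1.0 = 0.10 to 0.20 |

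**4. Simulation, also on assumed values.** Assumptions: 50 per arm, SD 1 at each visit, correlation 0.6 between visits, and a true hip-versus-sham difference of 0.60 SD. Loss occurs after the post-test and is likelier in players who improved less by then (log-odds 1.5 per SD unless stated). The 6-month column is the contrast of change scores among players who return. The last column is the post-minus-pre contrast that the plan describes.

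| Loss sham/knee/hip | Selective in | 6-month estimate | Post-minus-pre estimate |
|---|---|---|---|
| 30/20/10% | all arms | 0.517 | 0.602 |
| 30/20/10% | sham only | 0.464 | 0.596 |
| 20/20/20% | sham only | 0.511 | 0.604 |
| 20/20/20% | all arms | 0.598 | about 0.60 |
| 30/20/10%, log-odds 0.5 | all arms | 0.559 | about 0.60 |

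With no true difference, the nominal 5% pairwise test at 6 months rejects in roughly 7 to 9% of runs in the first three rows, 5.6% in the fourth and 5.8% in the fifth. The post-minus-pre test stays near 5%. A longitudinal model fitted to all 150 gives 0.60 in the first three rows. It must do so here, because loss was made to depend only on observed values.

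**The case against.** The strongest reply is that this is a condensed article. Handling of missing data is commonly left to the full protocol or SAP, neither of which is shown, and the article does not exclude imputation. Sizing a trial for attrition is also ordinary prudence and does not define an analysis set. Both points stand as far as they go: the absence of a missing-data section is no finding, and the sample size is not at fault, since the 20% loss was allowed for. They do not remove the conflict. The article makes a positive claim that all are analysed, and it names a test, powered on those who remain, that as described cannot deliver this.

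A reader might also infer that about 30 players drop out of the stated ANOVA and that its arm contrasts are biased. The documents do not support that:

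- The 20% loss is given for study end, while the stated ANOVA compares pre-test with the test right after 6 weeks.
- The simulated bias arises in a 6-month contrast among returners, a test that the analysis section does not describe. In the same simulation the post-minus-pre contrast is unbiased, because loss comes after the post-test.
- Even at 6 months the bias needs loss or selectivity to differ by arm. The plan assumes equal loss, and equal selective loss gives essentially none.

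It would also go too far to call the ITT claim false. The term is undefined, and the article is silent on how missing values enter.

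**Conclusion.** The point holds as a mismatch between a stated claim and a stated method. As described, the ANOVA analyses players with a follow-up test. The stated power agrees with that reading (79.8% at 40 per arm, against 88.5% at 50). The set at issue is up to 30 of 150 players at 6 months, and at most that number at the post-test if loss accumulates.

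Bias is possible, not shown. Under assumed differential loss it would be of the order of 0.05 to 0.20 SD. It is zero when loss and the gap between lost and retained players are the same in every arm. The documents do not allow a choice between these cases.

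Severity: should be fixed. It is not a must-fix, because neither the sample size nor the validity of the post-test comparison is shown to fail. Confidence is high on the mismatch and low on the size or direction of any bias.

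**What to change.** Replace the change-score ANOVA with one likelihood-based longitudinal model per outcome:

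- The response is KAM at pre-test, post-test and 6 months.
- Means are arm by visit, with a common pre-test mean across arms, which is justified because the pre-test precedes randomisation.
- The covariance is unstructured.
- The post-test and retention arm contrasts are both read from this model, with Tukey adjustment kept.
- A sensitivity analysis covers outcome-related missingness, for example a shift applied to the unobserved values of players missing through injury.

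Every randomised player with a pre-test then contributes, the stated retention hypothesis gets a defined analysis, and the ITT sentence can stand once the set is defined. Multiple imputation with a similar sensitivity analysis would also resolve the conflict.

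If the ANOVA is kept, describe it in both the analysis and sample-size sections as an available-data analysis with about 40 per arm, and drop the statement that all ITT participants are analysed.

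Cost: changed analysis wording, slightly more analysis work, and reliance on a missing-at-random assumption, which the sensitivity analysis is there to probe. No extra visits, staff or players are needed.
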